#### Economic evaluation

A cost-effectiveness analysis (CEA) will be performed from the company perspective. The time horizon will be 12 months, similar to the trial. The analysis will be performed according to the intention-to-treat principle. Missing data will be imputed using multiple imputation techniques. The primary outcome measurements in the CEA will be lifestyle (physical activity and daily fruit intake) and vitality (total score vitality scale UWES).

Two CEAs will be performed from the company perspective:

1) intervention costs together with savings as a result of reduced sick leave (absenteeism) and loss of productivity (presenteeism) will be compared to the obtained effects on the primary outcome measures lifestyle and vitality

2) intervention costs will be compared to the obtained benefits due to reduced sick leave and increased productivity.

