#### Step 6 - Evaluation plan

The (cost-) effectiveness of the lifestyle intervention developed in the preceding IM steps, will be evaluated in a randomised controlled trial (RCT) with two arms. During six months, employees in the intervention group will receive the lifestyle programme as described above. The control group will receive the same written information as the intervention group about a healthy lifestyle (physical activity, relaxation, fruit). Both groups will be measured at baseline, and after 6 and 12 months. The Medical Ethical Committee of both the VU University Medical Center (VUmc, Amsterdam, the Netherlands) and the Leiden University Medical Center (LUMC, Leiden, the Netherlands) approved the study protocol.

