### Work-related outcomes

Sick leave will be determined using the World Health Organization Health and Work Performance Questionnaire (WHO-HPQ) measuring loss of productivity due to decreased performance while at work (presenteeism) and sick leave (absenteeism). This questionnaire has shown good concordance with employer records of work absenteeism and critical incidents [58,59]. For the specific purpose of the economic evaluation, participants will be asked to complete the WHO-HPQ once every three months. Besides loss of productivity, the need for recovery after a working day will be measured using the 11-item 'need for recovery scale' from the Dutch version of the Questionnaire on the Experience and Evaluation of Work (Dutch abbreviation VBBA) [60].

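### Both planned company-perspective analyses combine self-rated performance at work with sick leave, and neither is planned on sick leave alone

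*Protocol article*

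**What the plan says.** Under Economic evaluation, the protocol article states that "Two CEAs will be performed from the company perspective", and that "The time horizon will be 12 months, similar to the trial".

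- In the first analysis the money side is "intervention costs together with savings as a result of reduced sick leave (absenteeism) and loss of productivity (presenteeism"), set against the effects on lifestyle and vitality.
- In the second, "intervention costs will be compared to the obtained benefits due to reduced sick leave and increased productivity".

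Under Work-related outcomes, a single instrument, the WHO-HPQ, supplies both components, "measuring loss of productivity due to decreased performance while at work (presenteeism) and sick leave (absenteeism"). It is self-completed: "participants will be asked to complete the WHO-HPQ once every three months". The support cited for it is this: "This questionnaire has shown good concordance with employer records of work absenteeism and critical incidents".

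Under Step 6 - Evaluation plan, "The control group will receive the same written information as the intervention group about a healthy lifestyle". Only the intervention arm also receives coaching visits, guided classes and free fruit.

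**The concern.** The two components do not have equal support. For sick leave the article cites agreement with employer records. For self-rated performance it cites nothing that supports converting a difference in ratings into paid hours.

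Workers cannot mistake their arm. Those in the intervention arm set goals, receive feedback from a coach and keep diaries, which could make them rate themselves more favourably whether or not their output changes. When such a rating is valued in money it is multiplied by paid working time, so a small difference can become a sizeable saving.

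If the combined saving is the only version produced, an employer reading the result cannot see how much rests on fewer sick days and how much on higher self-ratings. Cost-effectiveness is part of the study's stated aim, and the Conclusion expects companies to benefit if the programme is proven effective.

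**Working it through.** **The plan's own figures.** The article gives no economic figure to reproduce. Its only calculated figure is the sample size: 189 per group recomputes to 190, and 189/0.85 rounds up to 223. That has no bearing here, except that 189 is used as the group size in step 6.

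**1. Where presenteeism enters.** In the first analysis it reduces net cost. In the second it adds to the benefit. It is counted together with sick leave in both, and no third analysis is listed.

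**2. Contact time per worker.** From the sections Yoga, Workout and Personal Vitality Coach (PVC) Visits: 24 yoga and 24 workout sessions of 45 minutes, groups of at most 16, and three visits of 30 minutes.

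Staff hours per worker = 48 × 0.75 / group size + 3 × 0.5

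- Groups of 16: 36/16 + 1.5 = 3.75 h
- Groups of 8 (assumed half full): 36/8 + 1.5 = 6.0 h
- Groups of 4 (assumed): 36/4 + 1.5 = 10.5 h

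**3. Value of one rating point.** Assumed: a 0-100 rating, one point worth 1% of paid time, 46 working weeks, and equal hourly cost for staff and workers. Weekly hours run from 16 (the minimum under Study population) to 36 (assumed).

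- 16 h a week: 0.01 × 46 × 16 = 7.36 h a year
- 36 h a week: 0.01 × 46 × 36 = 16.56 h a year

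**4. Shift that matches contact time.** Shift = staff hours / (value of a point × years held).

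| Staff hours | Held 12 months, 36 to 16 h a week | Held 6 months, 36 to 16 h a week |
|---|---|---|
| 3.75 | 0.23 to 0.51 | 0.45 to 1.02 |
| 6.0 | 0.36 to 0.82 | 0.72 to 1.63 |
| 10.5 | 0.63 to 1.43 | 1.27 to 2.85 |

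With groups of 8 to 16 the range is about 0.2 to 0.8 points over 12 months and 0.5 to 1.6 over 6. Preparation, materials, rooms, fruit, organisation and any working time that participants give up are all left out.

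**5. Full programme cost.** With C the cost per worker, W the yearly wage cost and T the years the shift lasts, the break-even share of paid time is C/(W × T). All three are assumed: W from EUR 60,000 with T = 1, to EUR 20,000 with T = 0.5.

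- C = EUR 500: 500/60,000 = 0.8% to 500/10,000 = 5%
- C = EUR 1,000: 1.7% to 10%
- C = EUR 2,000: 3.3% to 20%

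On a 0-100 rating these percentages are points; on a 0-10 rating they are divided by ten. How many points are needed therefore has no meaning until the scale is fixed.

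**6. Precision.** With 189 per group and an assumed rating SD of 10 to 20 on 0-100, the unadjusted 95% half-width for an arm difference is 1.96 × SD × √(2/189) = 2.0 to 4.0 points. The step 4 shifts for groups of 8 to 16 all lie inside that.

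**7. The same comparison for sick leave.** The 3.75 to 6.0 h of step 2 is less than one working day of 7 to 8 h (assumed). EUR 500 corresponds to 500/(60,000/220) = 1.8 to 500/(20,000/220) = 5.5 fewer sick days per worker, assuming 220 working days a year.

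**The case against.** **Counting productivity is legitimate.** From the company's perspective, performance at work is a proper component of benefit, and nothing in the two sections is contradictory. This stands. The point is not that presenteeism should be removed.

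**The article is a condensed account.** Component breakdowns, valuation rules and sensitivity analyses may sit in a fuller plan. The article names the two components separately and does not say that only a total will be reported. The Abstract also lists productivity as a secondary outcome, so its effect may be analysed in its own right. This is fair, and the missing valuation rule is not criticised here. However, the article does enumerate its economic analyses, and both combine the two components. A separate effect estimate for productivity would not show whether the economic conclusion holds without it.

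**Stronger readings go too far.** A reader might infer that a shift of less than one point makes the programme pay for itself. The documents do not support that: scale, conversion, wage and programme cost are not given, step 4 recoups contact time only, its own range exceeds one point for a 6-month shift, and most of the fuller-cost cases in step 5 exceed one point on 0-100. A reader might also infer that presenteeism almost alone decides the sign of the result. Step 7 shows otherwise: against contact time, one fewer sick day would do as much.

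**Sick leave is self-reported too.** It comes from the same questionnaire and the same unblinded workers, so a result on absenteeism alone is not free of reporting bias. This stands. The cited agreement with employer records gives it better support but does not exclude reporting that differs by arm, so it should not license an unqualified claim.

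**Conclusion.** The point holds in limited form. Both planned analyses combine presenteeism with sick-leave savings, no version on sick leave alone is planned, and the cited validation does not cover the conversion of self-rated performance into money. Because workers can tell their arm, a response effect could offset a material part of programme cost and be read as a real saving.

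The size is illustrative only. About 0.2 to 0.8 points held for 12 months, or 0.5 to 1.6 held for 6, matches contact time of 3.75 to 6.0 h per worker, given the 0-100 scale, proportional valuation, 46 weeks, 16 to 36 h a week and equal hourly costs. Full programme cost would need a larger shift. The case for change rests on what the two analyses combine, not on any particular break-even value.

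**What to change.** Under Economic evaluation, keep both planned analyses and add the following:

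1. Run each a second time with absenteeism savings only.
2. Report the two versions side by side, with the absenteeism and presenteeism amounts shown separately.
3. Where a favourable result depends on including presenteeism, state that it rests on unblinded self-rated performance.
4. Note beside the absenteeism-only result that sick leave is also self-reported, though with cited concordance to employer records.

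The cost is one extra run of each analysis on data already due to be collected. No planned analysis is removed. The downside for the sponsor is that the economic conclusion may be less favourable.

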#### Process evaluation

The process of the intervention will be evaluated according to the key process-relevant variables: recruitment, older workers' attitude towards the intervention, fidelity, reach, dose delivered, dose received, and implementation [61,62]. The recruitment of the older workers is described elsewhere in this article (see 'recruitment of the study population'). The other key process-relevant variables will be assessed in four ways. First, at post-test the attitude towards the intervention will be indentified among the older workers' in the intervention group by asking their opinion about: 1) the intervention (VEP and PVC) as a whole; 2) the coaches' competence, and 3) the effect of the intervention on their own subjective vitality. Second, by means of registration forms filled in by the PVCs during each coaching visit, attendance to the coaching protocol (fidelity) will be assessed. Third, older workers in the intervention group will be asked to keep up a physical activity and fruit diary (reach, dose received, fidelity). Finally, the VEP sessions which will be delivered by the providers will be defined at pre-test (see 'design of the intervention'). Additionally, the fitness instructors will be asked to register the presence of the older workers at the guided group sessions (reach, dose received, fidelity). On the process evaluation, quantitative analyses will be performed.

## Discussion

The aim of this article was to describe the development, and the design of the intended evaluation of a lifestyle programme aimed at improving vitality in older workers. Applying the IM protocol to develop the lifestyle programme required time and effort. However, it helped us to carefully consider each decision concerning the development of the lifestyle programme, and planning the implementation and evaluation of the lifestyle programme. Therefore, we perceived the use of the IM protocol as a useful tool that has guided us through the development of our lifestyle programme.

### Strengths and weaknesses

The rising prevalence of older workers in the near future has created a need for cost-effective interventions that can prolong healthy employability of older workers. Consequently, one of the main strengths of the Vital@Work study is that this is the first RCT that evaluates the effectiveness of a lifestyle intervention in order to improve both the mental en physical components of vitality. Another strength of the Vital@Work study is that as a result of applying the IM protocol, we developed a lifestyle programme taking into account both a theoretical framework and the perspectives of older workers on: 1) lifestyle, 2) vitality and, 3) how vitality can be improved by a lifestyle programme. We believe that this will lead to a better compliance to the lifestyle programme and therefore improve the likelihood of effectiveness of the lifestyle programme. However, limitations of this study can be mentioned. First, in this study only older workers from academic hospitals were involved in the focus group interviews. Therefore, it is possible that the IM process led to a lifestyle programme, which is only applicable to this specific target population. Second, it should also be noted that implementation of this lifestyle programme is likely to be more difficult in hospital settings where fitness facilities are not available in the direct environment.

### Comparison with other studies

This type of lifestyle programme has not been evaluated in the setting of academic hospitals and in this target group (workers aged 45 years and over) yet. In addition, the combination of vigorous intensity physical activity with relaxation exercises (yoga), has not been reported before. However, several studies have reported the effectiveness of worksite physical activity programs on physical health (e.g. aerobic fitness, BMI) [63-68]. In addition, only a small number of studies reported the effectiveness of worksite physical activity programs on mental health (e.g. well-being) [66]. The effectiveness of a lifestyle programme involving physical activity on vitality has not been evaluated before. Yoga appears to be effective in reducing stress and improving health status in adults [28,69]. However, there are no studies available reporting the effect of yoga or relaxation exercises in (older) workers.

## Conclusion

The development of the intervention according to the IM protocol resulted in a Vital@Work lifestyle programme specially tailored to the needs of older hospital workers. To determine the (cost-)effectiveness of the lifestyle programme, we will examine vitality, lifestyle behaviour (physical activity, relaxation, and fruit intake), work factors and aerobic fitness in a RCT. Results of the RCT will be available in 2011. If proven effective, both companies and society will benefit from a effective tool to keep older workers healthy and vital and thereby contribute to prolonged healthy employability.
